## **PROJECT RATIONALE**

The origins of many mental health disorders are identifiable early in life, and early intervention programs are effective in significantly reducing lifetime impairments. This is a major achievement of the health sciences, but is offset by evidence that the most effective of these interventions (parent training for conduct problems, and CBT for anxiety disorders) only produce clinically significant change in ~50% of cases. Outcomes are considerably worse for children with multiple comorbid problems, particularly the neurodevelopmental disorders of ADHD and Autism Spectrum Disorders (ASD). Research from our clinic replicated in international samples has shown that individual differences in the epigenetic regulation of specific neurodevelopmental genes map onto and predict individual differences in social-Responsiveness, Emotional Attention, and Learning (REAL), which in turn, precisely characterise emerging psychiatric symptom patterns in children with complex mental health problems. Importantly, there are good reasons to expect that the interplay of these systems will predict the child's responsiveness to evidence-based intervention, and in turn, be altered by early intervention.

In order to improve treatments for child psychopathology, it is necessary to understand the neurodevelopmental processes that underpin clinical change during the periods in which the earliest features of mental health problems are most responsive to intervention. This study proposes to utilize progress in epigenetics and neurodevelopment to conduct a prospective longitudinal cohort study that will inform the treatment needs of individual children with complex presentations.

## **RESEARCH QUESTIONS AND AIMS**

This study has been designed to test the interplay of responsiveness to intervention, genetics and neurodevelopment to: a) confirm an emerging model of how epigenetic regulation of the major neurodevelopmental systems maps onto individual differences in comorbid symptom profiles before and after intervention; b) to examine how this regulation and mapping predicts individual differences in responsiveness of children to intervention that produces standardised and measurable improvements in the child caregiving environment; c) to examine how early intervention alters epigenetic regulation of the major neurodevelopmental systems and REAL phenomena, thus modifying risk versus protection for future development.

## **RESEARCH PROTOCOL:**

The research project will be a single site study and will take place at the Sydney Child Behaviour Research Clinic (SCBRC). Potential participants are the parents seeking help for managing behaviour problems in their child(ren).

### **Recruitment and Screening**

Initial contact (**intake form** and telephone information)

Extended screening assessment (for lengthy wait times):

1. Clinical Interview and the Diagnostic Interview Schedule for Children, Adolescents, and Parents (DISCAP) Assessment
2. Strengths and Difficulties Questionnaire (SDQ) (Goodman, 1997)
3. Amended Primary Attachment Style Questionnaire (PASQ; Salzman, Kunzendorf, Saunders, & Hulihan, 2013)
4. Methylation Assessment: Buccal Cell Collection

### **Participant Information and Consent**

1. Parent/Guardian
2. Teacher (sent with questionnaire link)

### **Pre-Treatment Assessment**

1. Clinical Interview and the Diagnostic Interview Schedule for Children, Adolescents, and Parents (DISCAP) Assessment
2. Online (or paper) Questionnaires
  - a. Parent/Caregiver Questionnaires
  - b. Teacher/Day care staff Questionnaires
  - c. Clinician Questionnaires
3. Computer Assessment: FACES Task
4. Family Observation Tasks and Psychophysiological Measures
5. Methylation Assessment: Buccal Cell Collection
6. Cognitive Assessment: The Peabody Picture Vocabulary Task (PPVT)

### **Treatment**

Parent Management Training: **[name] and [name]:** INTEGRATED FAMILY INTERVENTION FOR CHILD CONDUCT PROBLEMS: A Behaviour-Attachment-Systems Intervention for Parents

Mid-Point Methylation Assessment

### **Post-Treatment Assessment**

1. Brief Clinical Interview & DISCAP Assessment (Blind assessor)
2. Online Questionnaires
  - a. Parent/Caregiver Questionnaires
  - b. Teacher/Day care staff Questionnaires

- c. Clinician Questionnaires (dose and engagement measures)
- 3. Computer Assessment: FACES Task
- 4. Family Observation Tasks and Psychophysiological Measures
- 5. Methylation Assessment

### **Follow-Up Assessment**

Brief Clinical Interview and DISCAP Assessment (Blind assessor)

### **Recruitment and Screening:**

#### **Initial Contact:**

Families will be identified for recruitment and intake from our regular pool of self-referred families to the SCBRC. Typically parents have heard of the CBRC via schools, their GP or other health practitioner, or have found us during searches online or have responded to occasional notices we place in local magazines such as Sydney's Child that provide brief factual information about the research project. At first contact the parents are involved in a full 'arms length' information giving session involving details of the CBRC processes as well contact details for alternative non-research treatments should the parents prefer, and a screening assessment as to their suitability according to inclusion and exclusion criteria specified below, this takes approximately 15 minutes to complete. From this screening interview, likely eligible families are then allocated as potential participants for the research project and invited to attend an initial appointment to review information about the research project and consent documents. Those who wish to proceed and give full informed consent will undergo a comprehensive assessment. Extended screening assessments are offered to families where lengthy wait times prior to commencing treatment are expected. This is to ensure that ineligible families are not forgoing other treatment options while having to endure a lengthy wait for the initial assessment. The 1-hour face-to-face screening interview involves a semi-structured interview (Diagnostic Interview Schedule for Children, Adolescents, and Parents [Holland & Dadds, 1997]), a short behavioural screening questionnaire (the Strengths and Difficulties Questionnaire [Goodman, 1997]) and the collection of a buccal cell sample.

#### *Inclusion Criteria:*

Children aged between 2 to 8 years (no gender-based exclusion) who are assessed as having conduct problems using the following criteria: primary DSM-V diagnosis of Oppositional-Defiant or Conduct Disorder.

We adhere to the NIMH guidelines that research into the externalising disorders is compromised by exclusion of the major and naturally occurring comorbidities, thus ADHD, affective/anxiety disorders, learning problems, and mild autistic features are allowed if they are secondary and less severe than the conduct problems, and the child is not receiving or is stabilised on psychoactive medication in relation to them at the time of assessment.

#### *Exclusion Criteria:*

Exclusionary criteria include presence of a psychotic disorder, intellectual disability resulting in IQ 70, or a major medical disorder that has significantly interfered with school/family life, or family involvement in engaged in current legal issues including child custody disputes. Fluency in English will also be a criterion for inclusion due to the language format of the psychological measures.

### **Participant Information and Consent Forms**

Consent for the family to participate in the research will be obtained from the parents/guardians of the referred children. As described above families have been made aware of the CBRC as a research clinic prior to attending an initial appointment. At the initial appointment the family are then provided with further information about the research in the form of participant information forms as approved by HREC. Families are given time to review this information, seek clarification or discuss any questions or concerns with a member of the CBRC and also offered the opportunity to contact the project manager or chief investigator should that have any further questions prior to signing consent forms. All members of the CBRC who obtain consent from families, are given appropriate training in informed consent procedures by the project manager. Families also complete Consent to consult form prior to any member of the CBRC contacting a participant's school or daycare center as part of the research.

Teacher/child care worker consent to participate is sought using a written participant information form and consent form as approved by HREC which is sent to the teacher/child care worker once consent to contact this professional has been provided by the parent/caregiver.

### **Pre-Treatment Assessment**

- **Clinical Interview and Diagnostic Assessment:**

Parents/caregivers are invited to attend the first appointment at the CBRC without their child/ren and a clinical interview is conducted. Basic demographic and background details are also gathered during this appointment including child date of birth, age, gender, medication status, ethnicity of biological paternal and maternal grandparents (when known as required for epigenetic analysis) languages spoken at home, parent/caregiver age, gender, relationship to child, level of education, employment status and relationship between caregivers. This appointment also involves completion of appropriate sections of the Diagnostic Interview Schedule for Children, Adolescents, and Parents for DSM V (Avalon, Lechowicz, Hawes & Dadds, 2017), a measure of diagnostic status of the child. Parents/caregivers are then given either paper copies or online links to standardized questionnaires to complete.

- **Online/Paper Copy Questionnaires:**

- a. Parent/Caregiver Questionnaires*

- ADHD Rating Scales (DuPaul, 1991; McGoey, DuPaul, Haley & Shelton, 2007)
    - Strengths and Difficulties Questionnaire (SDQ) (Goodman, 1997)
    - Antisocial Process Screening Device (ASPD) (Frick & Hare, 2001)
    -

- Spence Child Anxiety Scale Parent Report and Pre-School versions (SCAS) (Nauta, Scholing, Rapee, Abbott, Spence & Waters, 2004; Spence & Rapee, 1999)
- The Autism Spectrum Quotient 10 Child Version (AQ10 Child) (Auyeung & Baron-Cohen, 2012)
- Parenting and Family Adjustment Scales (PAFAS) (Sanders, Morawska, Haslam, Filus & Fletcher, 2013)
- Parent Problem Checklist (Dadds & Powell, 1991)
- Parent Feelings Questionnaire (Deater-Deckard, 1996)
- The Depression, Anxiety and Stress Scales 21 Item Version (DASS 21) (Lovibond & Lovibond, 1995a)
- The Adapted Adverse Experiences Scales, Self and Caregiver Report Versions (Lechowicz, Roach, Fisher, Hawes & Dadds, 2017)
- Oppositional Defiant Disorder Irritability and Hurtfulness Dimensionality Measure
- Amended Primary Attachment Style Questionnaire (PASQ; Salzman, Kunzendorf, Saunders, & Hulihan, 2013)
- Evidence-based Time-out Implementation Scale (ETIS)
- Child Stress Disorders Checklist- Short Form (CSDC-SF; Enlow, Kassam-Adams & Saxe, 2010)

#### ***b. Teacher/Child Care Worker Questionnaires***

- ADHD Rating Scales (DuPaul, 1991; McGoey, DuPaul, Haley & Shelton, 2007)
- Strengths and Difficulties Questionnaire (SDQ) (Goodman, 1997)
- Antisocial Process Screening Device (ASPD) (Frick & Hare, 2001)

#### ***c. Clinician Questionnaires***

- Maltreatment Index (based on the Maltreatment Classification System by Barnett et al., 1993; 3 items rating levels of emotional and physical abuse and neglect)
- The Quality of Family Environment **Quality of the Family Environment** – a rating given by the clinician using a global scale to measure the quality of the family environment (Rey et al., 1997)

#### **• Computer Assessment: FACES Task**

UNSW FACES protocol (Facial Emotion Task) (Dadds et al., 2008, 2011) is a PowerPoint presentation in which participants identify the emotion of the face from the six target emotions of sadness, happiness, neutral, anger, fear and disgust, using 36 faces (6 actors x 6 emotions). The task has undergone extensive validation using child and adult samples. Dependent measures are eye gaze to the eye region of the stimuli faces, galvanic skin conductance and heart rate, and overall accuracy for each emotion under each gaze condition. Psychophysiological measures of the referred child including pupil dilation, eye gaze, galvanic skin conductance and heart rate are gathered during this task.

#### **• Family Observation Tasks and Psychophysiological Measures**

Structured observations of family interactions will be used to index emotion-related parent-child behaviours that are not possible for parents to accurately self-report on. Observational activities will comprise structured age-appropriate play interactions and a brief (e.g., 10-minute) emotion-reminding task (“talk about a happy time that you have all shared together and a sad time that you have all shared together”; Fivush, Marin, McWilliams, & Bohanek, 2009). Families will also view a small excerpt of the Lion King film, which is commonly used to elicit responses to emotional scenes. These activities are video recorded and coded. Psychophysiological measures of the referred child including pupil dilation, eye gaze, galvanic skin conductance and heart rate are gathered during the emotion elicitation exercise.

*Family observation tasks include:*

- a. Parent-child free play warm up exercise
- b. Emotion elicitation exercise (Control and Lion King videos)
- c. Parent-child emotion processing task
- d. Child only comprehension tasks
- e. Eye-love you task
- f. Parent Only Speech Sample Observation Tasks

- **Methylation Assessment: Buccal Cell Collection**

Buccal cell samples will be gathered from assenting children in order to measure functioning, via genetic sequencing, epigenetic markers, and peripheral levels, on the major neurohormonal systems of oxytocin/vasopressin, serotonin, dopamine, cortisol, and testosterone. Oracollect DNA OCR-100 swab kits will be used to collect Buccal cell samples however the children can refuse to participate in this. Participants are fully informed that these samples are only used for the neurohormonal assays and provide no information about paternity, health conditions, or other controversial information.

The samples will be collected by trained researchers and clinicians in the Child Behaviour Research Clinic using Oracollect DNA OCR-100 swab kits. However if children refuse to have a trained researcher or clinician collect the sample they will be given the option for parents to collect the sample should this be preferred. In such circumstances parents will be briefed as to the protocol for collecting Buccal cell using the swabs as employed by the researchers and clinicians.

- **Cognitive Assessment: The Peabody Picture Vocabulary Task (PPVT) (Dunn & Dunn, 2007)**

A developmental screening tool to estimate global abilities selected to be appropriate for the child’s age from Peabody Picture Vocabulary Test (PPVT) (Dunn & Dunn, 2007).

## **Feedback and Treatment**

Parents/caregivers are then invited back for a feedback and treatment planning session in which clinicians provide feedback on the assessment process and engage parents in a partnership empowering parents to engage with assessment findings and take part in intervention planning. Eligible families are then offered treatment. All families will be offered ‘treatment as usual’ there will be no control condition, no waitlist condition and no random allocation of cases within the proposed research project. The treatment comprises the Dadds and Hawes (2006) program, an evidence-based intervention with a long empirical history in the treatment of early-onset behavioural and emotional difficulties in children.

Treatment consists of approximately 6 to 10 x 1 to 1.5 hour treatment sessions that focus on empowering parents to better manage child behavioural difficulties, as well selected modules on parental mental health, marital adjustment and family communication and additional modules to address specific concerns such as management of anxiety and worry and emotional development or emotion socialization and school consultation where indicated for children and families.

**Mid-point Methylation Assessment:** Buccal Cell Collection (procedure as described above)

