### **Post-Treatment Assessment**

Post-treatment assessments are completed on average approximately 3 months after pre-treatment measures have been collected. This will involve completing the following assessments:

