## **DATA ANALYSIS:**

### **General Analysis Plan:**

The study is a prospective longitudinal cohort study and will take place from the point of approval and trial registration (likely to be approximately July 2017). The main science and analyses centre around using diagnostic grouping (Disruptive Behaviour Disorders, Anxiety and Depression, ADHD, Autism Spectrum Disorder) as the predictors and genetic and epigenetic data, neurohormonal levels, patterns of emotion processing, family interactions, cognitive impairments, and health outcomes being used as criterion variables. Typically we use Generalised Estimating Equations or similar multivariate methods with diagnostic groupings modelled as both categorical and dimensional variables in order to address the science of formal psychiatric categorical diagnoses, but also tackle the real world issue that diagnostics are rarely discrete and in fact, show high overlap and comorbidities and should be modelled as continuous and overlapping variables.

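### Aim (c) is worded as an effect of the intervention, but the design has no untreated comparison; reword it as change during treatment and use the wait-period buccal sample as a supportive reference for methylation

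*Protocol*

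**What the plan says.** Research Questions and Aims, aim (c), is "to examine how early intervention alters epigenetic regulation of the major neurodevelopmental systems and REAL phenomena". Feedback and Treatment says that every family is offered the same programme and that "there will be no control condition, no waitlist condition and no random allocation of cases within the proposed research project". The General Analysis Plan names the design openly: "The study is a prospective longitudinal cohort study". On timing, the Post-Treatment Assessment section says "Post-treatment assessments are completed on average approximately 3 months after pre-treatment measures have been collected".

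One untreated interval exists. Under Initial Contact, "Extended screening assessments are offered to families where lengthy wait times prior to commencing treatment are expected". That visit includes the DISCAP, "a short behavioural screening questionnaire (the Strengths and Difficulties Questionnaire [Goodman, 1997]) and the collection of a buccal cell sample"; the summary list under Recruitment and Screening adds the attachment questionnaire (PASQ). DISCAP, SDQ, PASQ and the buccal sample are all listed again at pre-treatment. The FACES task, family observation and psychophysiology first appear at pre-treatment.

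Data Analysis describes generalised estimating equations, regression and longitudinal mediation, using repeated measures, treatment dose and control variables such as age. It does not mention the interval from screening to pre-treatment.

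**The concern.** To say that treatment alters methylation or the REAL measures is a causal statement, and it needs some estimate of what would have happened without treatment. Here everyone is treated, so anything else that moves over the same 3 months moves together with treatment:

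- **Ageing**, in children of 2 to 8 years.
- **Assay or repeat-test drift** between visits.
- **Regression to the mean**, for symptoms, because children enter on a diagnosis of oppositional-defiant or conduct disorder.

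Age as a covariate adjusts for differences between children at a given time and does not remove the change each child undergoes. Treatment dose is not allocated, and the protocol itself lists family chaos, illness and employment as influences on engagement or on interference with treatment, so a dose relation is confounded.

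At stake is the wording of the conclusion. A real but untreated trend could be reported as an intervention effect on epigenetic regulation.

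**Working it through.** The protocol gives no figure for this contrast, so there is none to reproduce. Its sample sizes (225, 245 and 320) are for mediation, and the point does not depend on them; 225 serves only as a scale.

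**1. How easily drift looks like an effect**

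Inputs: N = 225 (Data Analysis). Assumed: pre-post correlation r = 0.6-0.8, zero treatment effect, two-sided 5% test of mean change, drift d in SD of the outcome.

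SD of change = √(2(1−r)), which is 0.894 at r = 0.6 and 0.632 at r = 0.8. Noncentrality = d·√N / SD of change.

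For d = 0.10: 0.10 × 15 / 0.894 = 1.68, and 0.10 × 15 / 0.632 = 2.37.

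| Drift (SD) | Significant, r = 0.6 | Significant, r = 0.8 |
|---|---|---|
| 0.10 | 39% | 66% |
| 0.15 | 71% | 94% |
| 0.20 | 92% | 99.7% |

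At N = 320, drift of 0.10 SD gives 51-81%. Without drift the rate would be 5%.

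**2. Which outcomes have an untreated interval**

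| Measure | Extended screening | Pre-treatment | Post-treatment |
|---|---|---|---|
| Buccal methylation | yes | yes | yes |
| SDQ | yes | yes | yes |
| DISCAP | yes (1997 version cited) | yes (2017 DSM-V version cited) | yes (1997 version cited, blind assessor) |
| PASQ | summary list only | yes | yes |
| FACES | no | yes | yes |
| Family observation, psychophysiology | no | yes | yes (fewer observation tasks) |

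The tasks that index the REAL constructs have no screening value, so the wait interval cannot act as a control for them.

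**3. Precision of the within-child comparison for methylation**

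Contrast = (post − pre) − (pre − screening) = post − 2·pre + screening. With equal intervals and equal correlation r between visits, its variance in SD units is (1 + 4 + 1)(1−r) = 6(1−r). Detectable difference at 80% power = 2.8 × √(6(1−r)/n). The number n with extended screening is not stated; 50-150 is assumed.

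| n | r = 0.6 | r = 0.7 |
|---|---|---|
| 50 | 2.8 × √(2.4/50) = 0.61 | 2.8 × √(1.8/50) = 0.53 |
| 150 | 2.8 × √(2.4/150) = 0.35 | 2.8 × √(1.8/150) = 0.31 |

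Data Analysis gives 0.3 for methylation without stating its scale, so the comparison is rough. The contrast would be near or short of adequate power across this range.

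**4. Why the same contrast fails for symptoms**

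Waiting families are checked for eligibility on DISCAP and SDQ at extended screening. Suppose they are selected there at about 1.6 SD above the mean (assumed) and treatment has no effect. Expected change over the wait is −1.6(1−r), and expected change over treatment is 0. The contrast is then +1.6(1−r):

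- r = 0.6: 1.6 × 0.4 = 0.64 SD
- r = 0.7: 1.6 × 0.3 = 0.48 SD
- r = 0.8: 1.6 × 0.2 = 0.32 SD

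A true benefit of that size would be hidden. Renewed selection at pre-treatment would change the split between intervals without guaranteeing that the bias cancels.

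**The case against.** **The single-arm cohort is deliberate and declared.** This stands. An uncontrolled cohort is a legitimate choice, and the fault lies in the causal wording of aim (c).

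**The error rates belong to a test the protocol does not name.** This stands. The planned models are estimating equations, regression and mediation. Uniform drift enters the mean and does not by itself create an association or an indirect effect. The rates in the first table show only the risk in reading mean change as a treatment effect.

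**The analysis plan may use the wait interval.** This stands as well. The statistical analysis plan is not at hand, so the protocol's silence on the interval is not a defect in itself. A reader might infer that an available control is being wasted; the documents do not show that. The mismatch between aim (c) and the design remains either way, since no analysis plan can supply an untreated arm.

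**The wait interval could be taken as a control for all of aim (c).** A reader might infer this, but the documents do not support it. REAL tasks are absent at screening, symptom contrasts are biased by selection at screening, and for DISCAP the cited version and stated blinding differ between visits. Precision of 0.27-0.39 SD can be calculated for 50-150 screened children out of 225, but only by borrowing from children without a screening visit and assuming that their course matches that of the waiting families.

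**Regression to the mean could be set against the improvement of 0.5 in Data Analysis.** That figure concerns emotional attention, responsiveness and learning. Entry is on a conduct diagnosis, so the comparison does not carry over.

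**Conclusion.** The point holds in a limited form. Aim (c) promises a conclusion about what the intervention alters, and the design supports only a description of change during treatment. Under a simple pre-post mean test, an assumed drift of 0.10 SD would be significant in 39-66% of studies at N = 225 with no treatment effect. This rests on assumed correlations of 0.6-0.8 and an assumed drift, neither of which the protocol gives.

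The untreated interval can help with methylation alone, as supporting evidence. It comes from a non-random subset whose size and length of wait are not stated. Its detectable difference of 0.31-0.61 SD assumes 50-150 children, correlations of 0.6-0.7 and a wait as long as the treatment interval.

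A reader might conclude that the study cannot proceed without a control arm, or that a wait-controlled contrast must become the main analysis of every outcome. Neither follows: aims (a) and (b) are not affected by this point, and the contrast is unsuitable for symptoms and unavailable for REAL tasks. This should be fixed, and it is a cheap improvement.

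**What to change.** 1. Reword aim (c) and the conclusions drawn from it as *change during treatment*. This matters most for the REAL measures, which have no untreated reference at all.
2. For methylation, pre-specify a supportive within-child comparison in the extended-screening families: change per month from pre- to post-treatment against change per month from extended screening to pre-treatment. Keep the pre-treatment visit as the treatment baseline. Report the number of families, the length of wait and the confidence interval.
3. Do not make this the main contrast for SDQ or DISCAP. If it is shown for them, state the direction of the bias and the differences between visits in DISCAP version and blinding.

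Cost: text in the protocol and one added analysis, with no new visit, sample or change to care. The drawback is that the comparison is non-randomised and imprecise, so a null result from it would not show that treatment has no effect.
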